### Structured clinical interview

Demographic information (age, race, sex at birth, self-identified gender) will be collected along with detailed medical history, including visceral disease diagnosis, family and menstrual history (for female at birth participants), history of surgeries, medications, and disease activity scores (see Supplementary Information for genetic sampling criteria).

The participants will also fill the following questionnaires:

1Brief Pain Inventory-Short-Form [21].2Body maps to indicate locations of pain (see Supplementary Information for examples) [22,23].3McGill Pain Questionnaire [24].4O’Leary-Sant Interstitial Cystitis Questionnaire (IC-Q) [25].5Pelvic Pain Urgency/Frequency Patient Symptom scale [26].6ACR 1990 Fibromyalgia Diagnostic Criteria [27].7ACR 2016 Fibromyalgia Diagnostic Criteria [28].8Malmo POTS Score (MAPS) [29].

Standard measurements, including weight, height, pulse, and blood pressure, will be taken [30].

### Wearable sensor baseline

Prior to subsequent assessments, participants from Extreme Visceral Pain and Healthy Controls cohorts will be fitted with a Sibel Discovery *ANNE* chest sensor to establish a physiological baseline. The sensor will be applied at rest to collect continuous data including heart rate, skin temperature, and movement parameters. This baseline will serve as a reference point for future longitudinal comparisons and will contextualise results from later stages of the study, including physical examination, quantitative sensory testing, and bio-sampling.

### Quantitative sensory testing

Quantitative Sensory Testing (QST) will be performed to check for neuropathies [31,32] in all cohorts. Tests will include warm and cool detection with a contact heat thermode, vibration sense using a tuning fork, and touch sensitivity with von Frey filaments. Pressure pain thresholds will also be tested using an algometer. In cases where individuals lack expected pain sensitivity, a specialized protocol will be used to further assess painlessness (REC 12-EE-0369) [18].

### Bio-sampling

Participants from Extreme Visceral Pain and Lack of Visceral Pain cohorts will be asked to provide various samples to help researchers understand the similarities and differences in how conditions affect chronic visceral pain. Participants may choose to donate some samples while opting out of others, including those used in research involving non-human models.

**Whole blood:** Up to 50 mL of whole blood will be obtained through venepuncture. 5 mL of the whole blood sample will be sent for DNA extraction at the Department of Medical Genetics, University of Cambridge. 40 mL of the whole blood sample will be processed and sent for analysis and long-term storage to the Wolfson Sensory, Pain and Regeneration Centre at King’s College London. 5 mL of the whole blood sample will be processed and sent for long term storage to the Centre for Reproductive Health, Institute for Regeneration and Repair, University of Edinburgh.

**Urine:** Participants will collect mid-stream urine samples using a sterile device (UNI0054 or Colli-pee) at home or in the clinic, returning the samples via post. The urine sample will be sent to the Centre for Reproductive Health, Institute for Regeneration and Repair, University of Edinburgh.

**Vaginal swab:** Participants will self-collect a low vaginal swab (using BBLtm culture Swab MaxV or OMNIgene•vaginal | OMR-130), following provided instructions, and return the sample by post. The vaginal swab samples will be sent to the Centre for Reproductive Health, Institute for Regeneration and Repair, University of Edinburgh.

**Faeces:** Participants will collect up to three samples (using OMNIgene•GUT | OMR-200) at home and send them by post to the Cambridge Institute for Medical Research, University of Cambridge.

### Wearable sensors

Participants from Extreme Visceral Pain and Healthy Controls cohorts will use two types of wearable sensors to monitor physiological data:

**Chest *wearable sensor*:** The Discovery *ANNE* Chest System is a flexible, rechargeable sensor worn on the upper chest for up to 16 hours daily over 30 days. It tracks heart rate, respiratory rate, skin temperature, and activity level. Participants will answer two questions daily via a mobile app in a tablet linked to the sensor: “Have you had a visceral pain flare today?” and “Have you changed or cancelled an activity due to visceral pain today?”. To encourage adherence to the wearable sensor usage protocol, instructional videos on how to wear the devices were made publicly available and shared with participants (see Supplementary Information). Additionally, Fig 3 is printed and shared with the participants to provide a visual guide with key steps for sensor setup, syncing, and daily use.

**Fig 3 pone.0350169.g003:**
[figure not shown]
Wearable Sensor Deployment and Participant Instructions for the ADVANTAGE Study. Chest-worn respiratory sensor and wrist-worn physiological monitor setup for 4-week continuous data collection from Extreme Visceral Pain and Healthy Controls cohorts. Diagram illustrates wireless charging station, 2-metre Discovery App tablet sync range for data upload, daily reapplication protocol (shower before reattachment, correct orientation), and smartphone app for *ad libitum* pain reporting (0-10 Likert scale). Key operational constraints shown: non-waterproof (daily removal for showering), medical imaging contraindication (X-ray/MRI interference), QR code access to instructional videos. Ensures compliance for primary endpoint analysis correlating respiration rate, HRV, activity, and posture against real-time pain scores.

**Upper limb *smartwatch*:** The wrist-worn device (ActiGraph GT9X Link or GENEActiv, for Cambridge and Edinburgh sites, respectively) records limb movement and position continuously for up to 90 days. Data is downloaded after the wearable is returned, either by post or during a follow-up visit.

***ADVANTAGE Diary* remote mobile app questions during wearable sub-study:** Pain severity will continue to be recorded through the *ADVANTAGE Diary* app using the same 11-point scale as with the cohort classification stage. Participants will also receive daily reminders, and those who report pain will be asked additional questions: “How worried are you about that pain?” (rated 0–10), and “What is the position of your body right now?” (options include sitting, standing, lying down, squatting, moving actively). Those using the smartwatch and the *ADVANTAGE Diary* remote mobile app will be invited to continue for up to 90 days or until the smartwatch battery runs out after the follow up visit.

### Data management

Data will be collected using web-based database applications such as REDCap (Research Electronic Data Capture) and may also include paper-based Case Report Forms (CRFs). Where no prior record exists, the CRF will serve as the source document, and data will be directly entered into the CRF or REDCap. Clinical phenotype data will be extracted from hospital records by the clinician or research nurse and securely entered into the encrypted REDCap database. This database, developed by the ADVANTAGE research team, will be stored within the University of Cambridge’s safe haven.

Core data will include information from structured clinical interviews, physical examinations, questionnaires, and QST testing. Personal data (such as first/last names, email addresses, and NHS or CHI numbers) will also be collected, kept in the safe haven, and linked to each participant via a unique study ID generated by REDCap. This ID will be free of personal identifiers and consist of a 6-character string (e.g., LFWXAY). Access to the safe haven will be restricted to specific research team members authorized by the Chief Investigator. All other data (such as wearable sensor data) will be anonymized and stored outside the safe haven, linked only to the study ID.

Any fully anonymized material or data generated by the study (excluding personal data) may be transferred to external parties via a Data or Material Transfer Agreement. Identifiable information will be stored for up to one year after the study’s conclusion to ensure participant safety and to allow for regulatory review. Fully anonymized data (raw or processed) may be retained for up to five years beyond the study’s completion.

### Sample management plan

Any remaining samples from the study will be stored anonymously for use in future ethically approved research.

Serum samples will be linked-anonymized and stored at −70 to −90°C in secure, card-access-only freezers for the duration of the study. These samples will be sent to the Wolfson Sensory, Pain and Regeneration Centre at King’s College London for analysis and storage. Autoantibodies will be purified from the serum to investigate their autoreactivity, including whether they bind to tissues in mice and humans. Tests will be conducted to determine if serum or purified antibodies can replicate symptoms experienced by participant donors using behavioural tests in mice. The antibody-depleted serum will also be stored at −70°C and used for biochemical assays, such as measuring inflammatory markers. In addition, some serum samples will be sent to the Centre for Reproductive Health, Institute for Regeneration and Repair, University of Edinburgh for further research into chemicals and proteins associated with chronic pain.

Whole blood samples will be linked-anonymized and sent to the Department of Medical Genetics at the University of Cambridge, where DNA will be extracted and stored at −70 to −90°C in secure freezers. Using advanced or future-developed laboratory techniques, we will study changes in genomes that could influence the development or prevention of visceral pain. These linked-anonymized DNA samples will be fully anonymized upon study completion and may be stored indefinitely for future research.

Urine and vaginal swab samples will be linked-anonymized and sent to the Centre for Reproductive Health, Institute for Regeneration and Repair, University of Edinburgh. These samples will be stored in secure, card-access-only facilities and used for future ethically approved studies aimed at understanding chronic visceral pain. Specifically, we will study the role of hormones and bacteria in the body from these. Upon study completion, the linked-anonymized samples will be fully anonymized and may be stored indefinitely for future research.

Faecal samples will be linked-anonymized and sent to the Cambridge Institute for Medical Research at the University of Cambridge. They will then be batch-processed by a commercial collaborator for analysis. The analysis will help us better understand the role of gut bacteria in chronic visceral pain. These samples will be fully anonymized after the study and may be stored indefinitely for future research.

### Data analysis plan

The primary goal of this study is to investigate chronic visceral pain across different phenotypes using wearable sensor data and genetic analysis. While our broader objectives focus on generating exploratory insights into the genetic regulation of visceral pain, we aim to prioritize a well-powered, clinically useful outcome based on wearable sensor data, which will allow us to test a hypothesis within a smaller sample size.

### Primary endpoint analysis

The primary hypothesis we will test is that specific physiological parameters measured by wearable sensors (such as heart rate, physical activity, or respiration) will associate with self-reported pain intensity and specific body postures, such as sitting or lying down. We hypothesize that:

Higher pain scores will associate with reduced mobility and specific postures (e.g., sitting or lying down).Wearable sensor data will provide objective measures that can predict or associate with self-reported pain intensity.

This hypothesis will be tested using a linear multiple regression model with the following four predictors:

1Heart Rate Variability2Physical Activity (as measured by accelerometery)3Posture (sitting, standing, lying down)4Mean daily respiration rate

We expect that a sample size of n = 100 exclusively for the wearable sub-study provides 80% power to detect a moderate effect size (f² = 0.12 or larger) at p < 0.05, assuming four predictors.

For the primary analysis, we will fit a multiple linear regression model with mean daily visceral pain intensity as the dependent variable and the four pre-specified wearable predictors as independent variables. Model diagnostics will include inspection of residual-versus-fitted plots, Q–Q plots, and tests to assess both normality of residuals and multicollinearity between predictors. If substantial non-linearity or heteroscedasticity is detected, we will explore appropriate transformations of predictors or outcome while retaining the same pre-specified predictor set. All analyses will be conducted using validated statistical packages (either in R or Python), and the final model specification, diagnostics, and code will be documented to support reproducibility.

These four predictors were selected *a priori* based on established physiological relationships with pain states. Heart rate variability reflects autonomic nervous system engagement known to correlate with pain perception and flare severity in visceral pain syndromes [33–35]. Physical activity reduction is an established behavioural marker of pain avoidance and flare severity [36–38]. Posture is critical in visceral pain as many patients adopt characteristic positions during flares (e.g., lying down during endometriosis flares) [39,40]. Respiration rate was selected over alternative markers (such as skin temperature or sleep metrics) because: (i) it is directly modulated by nociceptive signalling through brainstem-vagal pathways critical to visceral pain processing [41,42], (ii) respiratory patterns are objectively measured with high fidelity by our chest-worn sensors, (iii) respiration is feasible for continuous long-term monitoring without imposing additional participant burden. Skin temperature was not selected due to confounding by environmental factors, and sleep metrics, whilst potentially informative, require longer data epochs incompatible with our primary real-time flare detection objective. No additional predictors will be included in this primary model.

We will use the correlation coefficients and regression analyses described to evaluate associations between these parameters and self-reported pain intensity, measured on an 11-point Likert scale (0–10). Confounding variables such as age, diagnosis, and occupation will not be included in the primary model but will be explored in sensitivity analyses.

Where multiple days of valid wearable data are available per participant, we will first derive participant-level mean values for each predictor over the observation period and use these aggregated values in the primary regression model; this avoids inflating the effective sample size and simplifies interpretation at the participant level. Day-level models will also be explored by using linear mixed-effects models with a random intercept for participant data.

Given that not all participants from the Extreme Pain cohort will use the wearables, the total number of participants we aim to recruit in the Extreme Pain cohort needs to exceed 100 to ensure adequate statistical power for this primary hypothesis. Healthy controls are not included in this confirmatory analysis, as they are unlikely to report sufficient pain scores for reliable modelling.

Missing data will be addressed using a complete-case analysis approach. No imputation methods will be applied for the wearable sensor data. Analyses will be restricted to participants with valid data for all variables included in the respective models. The extent and pattern of missingness will be reported descriptively. Where appropriate, we will perform sensitivity analyses to assess whether the exclusion of participants with missing data materially affects the results. For transparency, we will report the number of participants and observations included and excluded from each primary and sensitivity model in a CONSORT-style flow diagram and accompanying table. We will also present summary characteristics of participants with and without complete wearable data to allow readers to assess potential selection bias. This approach is justified by the observational nature of the study and the focus on real-world feasibility and data integrity.

This pre-specified analysis aligns with the SPIRIT recommendations for defining and justifying primary hypothesis-testing outcomes in clinical research protocols. All other objectives in this study, including genetic, immunological, and clustering analyses, are exploratory and will be pursued as hypothesis-generating efforts as more data becomes available.

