### Aims and endpoints

The overarching aim of this study is to deepen our understanding of chronic visceral pain by identifying and evaluating the genetic, molecular, and physiological mechanisms that contribute to this condition. We will examine these mechanisms across different participant groups, including those with extreme visceral pain, those with a lack of expected pain despite visceral disease, and healthy controls.

Our **primary objective** is to look for physiological markers (such as changes in movement, heart rate, and postural patterns) that predict or associate with visceral pain flares by examining data from wearable sensors. This will provide objective, real-time insights into how visceral pain affects day-to-day activities, and will be tested using a pre-specified statistical model and is central to the confirmatory aspect of the study.

In addition, we will undertake a series of **secondary/exploratory objectives**, which include the following key areas of investigation:

1**Genetic insights:** We aim to identify and characterize the genetic factors that underlie chronic visceral pain in specific participant cohorts, which include individuals with conditions like polycystic kidney disease, inflammatory bowel disease, chronic pancreatitis, endometriosis, and painful bladder syndrome.2**Spatial and temporal pain mapping:** We will create detailed maps of where and when individuals experience visceral pain. This includes analysing the frequency and intensity of pain reported by participants using a remote mobile app and wearable sensors that track body movement, posture, heart rate, and breathing.3**Biological sample analysis:** We will collect a variety of biological samples—blood, urine, low vaginal swabs, and faeces—from participants to explore pain mediators and modulators. This will include testing human serum in passive transfer experiments using mice to better understand the role of autoantibodies and other pain-related factors [19].4**Comparing pain groups:** We will compare participants with high levels of visceral pain, regardless of disease activity, to those with little or no visceral pain despite having active disease. These groups will be contrasted with healthy control subjects to uncover key differences in pain experience and physiology.

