### Baseline on site visit assessments

#### Remote mobile app.

The *ADVANTAGE Diary* remote mobile app will be used to intermittently track pain experiences [20]. Participants will be asked to download the app from major platforms (e.g., App Store, Play Store) and will be registered by the study team with a unique study identifier. Over a period of up to 6 weeks, individuals will use the app to rate their visceral pain by responding to the prompt, “Please rate the severity of your pain right now,” on an 11-point Likert scale. The scale ranges from 0, representing no pain, to 10, representing the worst pain imaginable. This will specifically relate to their visceral pain. Individuals are encouraged to record their pain daily, and during painful “flares” as needed. The *ADVANTAGE Diary* remote mobile app will send reminders, no more than once daily, for these ratings. During this 6-week period, participants reporting a pain score of 4 or higher on two separate occasions at least one week apart will be placed in the Extreme Pain cohort, while those with scores below 4 will join the Lack of Visceral Pain cohort. This distinction is made to simplify cohort classification and study procedures. It does not imply that participants with scores below 4 are pain-free, nor that a score of 4 or 5 necessarily represents extreme pain; rather, it provides a practical framework for grouping participants based on pain intensity levels.

In exceptional cases where individuals face difficulties accessing the app due to IT literacy or lack of smartphone access, a telephone screening will be arranged. The study team will ask participants to rate their pain over the phone, using the same 0–10 scale.

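### The planned models can show that sensor data and pain go together, but not that sensor data predict pain, because none is stated to place sensor data before pain

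*Protocol article*

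**What the plan says.** In the Protocol article, Aims and endpoints, the primary objective is physiological markers "that predict or associate with visceral pain flares by examining data from wearable sensors", and this is called central to the confirmatory part of the study. The primary endpoint in the same section repeats the either/or wording for pain levels. Primary endpoint analysis includes the hypothesis "Wearable sensor data will provide objective measures that can predict or associate with self-reported pain intensity" and, when explaining why sleep metrics were left out, describes detecting flares in real time as a primary objective.

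The models are described under Primary endpoint analysis. The primary one is a multiple linear regression of mean daily pain on four sensor variables. Each variable is averaged per participant over the monitoring period, and the model is closed to further predictors. Beyond that, "Day-level models will also be explored by using linear mixed-effects models with a random intercept for participant data". No lag, alignment window or prior-pain term is given.

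The same section justifies the predictors: "Physical activity reduction is an established behavioural marker of pain avoidance and flare severity", and posture is included because patients take up particular positions during flares. Pain is rated in response to "Please rate the severity of your pain right now" (Baseline on site visit assessments, Remote mobile app), daily and additionally during flares.

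**The concern.** To say that a marker predicts pain is to say that it carries information before the pain is reported. A period mean has no before and after. A whole-day sensor mean set against that day's pain includes hours after a rating and is complete only when the day is over. If patients rest because they hurt, both analyses will tend to show low activity alongside high pain, whether or not activity carries any advance signal.

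What is at stake is the conclusion drawn. Because the objective joins prediction and association with an *or*, a single contemporaneous slope could be reported under either label. A reader might then take a consequence of pain for an early-warning marker.

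**Working it through.** **1. The plan's own figure.** The plan states that "a sample size of n = 100 exclusively for the wearable sub-study" gives 80% power at f² = 0.12 with four predictors. For the overall F test, u = 4, v = 100 − 4 − 1 = 95 and λ = f²·n = 0.12 × 100 = 12. The noncentral F distribution gives 78.0%; 80% needs n = 105, or f² ≈ 0.125 at n = 100. This is a near miss, and nothing below depends on it.

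**2. Time order in each described analysis.**

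- Primary regression: one mean per person on both sides, so no order. Its predictor set is closed, so a lag or prior-pain term cannot be added without contradicting the text.
- Day-level mixed model (exploratory): time-resolved, but no lag or earlier-pain term is stated.
- Time-series work listed among the secondary endpoints (Aims and endpoints): self-reported ratings only.
- Daily flare question (Wearable sensors): enters no described model.

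The rationale for activity and posture runs from pain to sensor.

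**3. Illustration with no predictive content.** From the protocol: 100 participants and 4 weeks (28 days). Assumed: between-person and within-person pain SD 1, activity noise SD 1 at both levels, day-to-day pain autocorrelation ρ = 0, 0.3 or 0.6, and slope b = −0.2 or −0.5. There were 400 replicates per setting.

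- Pain: p(t) = μ + e(t), with e(t) = ρ·e(t−1) + innovation.
- Activity: a(t) = person effect + b·p(t) + noise. Activity never enters later pain.

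Expected within-person results:

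- Same day: slope of pain on activity = b/(b² + 1). This is −0.2/1.04 = −0.19, or −0.5/1.25 = −0.40.
- Previous-day activity, unadjusted: the covariance with today's pain is b·ρ, which is not zero when ρ > 0.
- Previous-day activity, adjusted for previous-day pain: p(t) given p(t−1) depends only on the innovation, so the slope is 0.

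Simulated proportion significant at 5%:

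| Model | Result |
|---|---|
| Aggregated primary model (activity plus three noise predictors, overall F test), b = −0.2 | 29–33% |
| Same, b = −0.5 | 98–99% |
| Same, b = 0 (ρ = 0.3) | 3.5% |
| Same-day, within person | 100% |
| Previous day, unadjusted, ρ = 0 | about 5% |
| Previous day, unadjusted, ρ = 0.3–0.6 | 88–100% |
| Previous day, adjusted for previous-day pain | 3–7% |

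The simulation error around 5% is √(0.05 × 0.95/400) = 1.1 points, so 3–7% is consistent with nominal. These within-person runs treated person means as known. A separate simulation estimated the within-person regression with person-clustered variance (ρ = 0.3, activity falling after the rating by 0.10–0.30 SD per SD of pain, 500 data sets per setting). It gave 94–100% for the same-day slope and 4.4–5.6% for the adjusted lag.

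**4. Would a sensor window ending at the rating do instead?** Take 16 wear hours a day, a rating after hour 4, and activity purely a consequence of current-hour pain (slope 0.1–0.3). With hour-to-hour pain autocorrelation of 0.5–0.9 (assumed), the pre-rating window was significant in 61–100% of trials, and in 63–100% after adding previous-day pain. A separate run gave about 65–100%. At zero hourly autocorrelation it was about 5%. Such a window therefore picks up behaviour from pain that began before the rating, and the protocol invites ratings during flares.

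**The case against.** The strongest reply is that the confirmatory claim is association. The Abstract speaks of correlation, and Primary endpoint analysis says the parameters are expected to associate with pain. Aims and endpoints says the objective should show how pain affects daily activity, which is the pain-to-rest direction, and gives quantifying and monitoring pain as the use. Detection is not forecasting: lying down because of pain is a legitimate marker that pain is present. All of this stands. In the simulation pain really does lower activity, so a significant same-day slope is a true positive for association.

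A reader might go further and infer that the primary analysis is invalid, or that resting patients are bound to appear as a predictive marker. The documents support neither. The association test needs no time order, and in the aggregated model the result depends on effect size (29–33% against 98–99%).

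It is also fair that an exploratory mixed model may be specified more fully in a plan not shown, so its timing is unstated rather than fixed as same-day. That does not help the primary model, which is fixed here and cannot order events.

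The reply does not rescue the word *predict*. It stands in the objective, the endpoint and the hypothesis, and no described analysis can answer it.

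**Conclusion.** The point holds in limited form. As described, the models support association and concurrent monitoring; the predictive half of the primary objective cannot be answered from them. No primary estimate, test or sample size is affected. The conclusion about time order rests on the text alone. The rejection rates illustrate it under assumed slopes, SDs and autocorrelations, because the documents give none.

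One limit applies to the remedy as well. If ratings capture the previous day's pain incompletely, previous-day sensor values can carry information about the pain that was missed. An adjusted lagged association therefore means advance information, not that the sensor change causes pain. This is a worthwhile, inexpensive improvement rather than a defect that blocks the analysis.

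**What to change.** 1. Keep the primary model unchanged. State that its slopes, and any same-day slopes, are reported as association only.
2. In the day-level analysis under Primary endpoint analysis, add a model of each day's pain on the previous day's values of the same four predictors, adjusted for the previous day's pain, taken as the mean of all that day's ratings. The adjustment is essential: a lag alone fails when pain is autocorrelated.
3. Use *predict* only for markers supported by that model, and define it as advance information, not causation.
4. Do not treat a sensor window ending at the rating as evidence of prediction. It may be reported as detection.

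The cost is wording and one extra exploratory model on data already being collected; only dates are needed. Days without a valid preceding day drop out, and the lagged result remains exploratory. Study status says no analysis has been performed, so this can still be pre-specified.

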**Table 1 pone.0350169.t001:** Inclusion and Exclusion Criteria for the Extreme Visceral Pain and Lack of Visceral Pain cohorts. Comprehensive eligibility matrix for the remote mobile app sub-study, wearable sensor sub-study, and bio-sampling sub-study. Common criteria: ≥ 18 years, UK-based, informed consent capable. Sub-study exclusions ensure safety (pacemakers, contact dermatitis), feasibility (travel restrictions), and cohort purity (no confounding pain conditions). Criteria support n = 350 total recruitment with n = 100 wearable sub-study power (80% power).

Sub-study	Inclusion Criteria	Exclusion Criteria
Remote mobile app	Pain, or lack of pain, associated with one or more of the specified visceral diseases or chronic pain conditions as diagnosed by an expert NHS medical professional.	Not able to fulfil the inclusion criteria
	Able to provide informed consent electronically	
	Aged 18 years and over	
	Living in the UK	
Wearable sensor	Able to fulfil the inclusion criteria of the remote mobile app sub-study	Unable to attend or visit the research site.*
		Travel abroad in the plan duration of wearable sub-study
	Have completed and adhered to the procedure in remote mobile app sub-study	
		Unable or unwilling to use body sensor for any reason (e.g. contact dermatitis over wear zone, implanted pacemaker or defibrillator, allergy or hypersensitivity to nickel)
Bio-sampling	Pain associated with one or more of specified visceral diseases or pain condition diagnosis by an NHS medical professional	Unable to attend or visit the research site.*
	Meet further clinical criteria for genetic sampling and analysis (see Supplementary Information)	
	Able to provide informed consent	Not able to fulfil the inclusion criteria
	Aged 18 years and over	
	Lives in the UK	

** Participants are eligible for the study regardless of their location, as long as they are willing and able to travel to the research site.*

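### The stated 80% power at n = 100 and f² = 0.12 is 78% for four model terms and 74% if three-category posture takes two; it also requires all 100 to be analysable

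*Protocol article*

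**What the plan says.** The power statement is in the Primary endpoint analysis section of the protocol article: "n = 100 exclusively for the wearable sub-study provides 80% power to detect a moderate effect size", with the remaining inputs given as "f² = 0.12 or larger) at p < 0.05, assuming four predictors". The Table 1 caption repeats the claim: "Criteria support n = 350 total recruitment with n = 100 wearable sub-study power (80% power".

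The same section describes the model the claim belongs to: "This hypothesis will be tested using a linear multiple regression model with the following four predictors". The four are heart rate variability, physical activity, posture and mean daily respiration rate. Posture is listed with three categories (sitting, standing, lying). How it is coded is not stated.

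Each participant contributes one record, because "we will first derive participant-level mean values for each predictor over the observation period and use these aggregated values in the primary regression model". On missing data the section says "Missing data will be addressed using a complete-case analysis approach", rules out imputation of the sensor data, and adds "Analyses will be restricted to participants with valid data for all variables included in the respective models". It requires the Extreme Pain cohort to be larger than 100 because some of its members will not use the wearables. It excludes Healthy Controls from the confirmatory analysis, although the Wearable sensors section has them wear the devices too.

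**The concern.** All the inputs for a power calculation are printed, so the figure can be checked, and it does not come out at 80%. Two features of the described analysis could lower it further. A predictor with three categories normally uses two degrees of freedom, while the calculation counts it as one. And 100 is given as the size of the wearable sub-study, while the model is fitted only to participants with valid data on every variable.

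This is the only power claim for the only confirmatory analysis, which the Data analysis plan section presents as well powered. If the true figure is lower, the chance of missing the stated effect is larger than readers are told, and a null result would be given more weight than it deserves.

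**Working it through.** **Inputs.** From Primary endpoint analysis: n = 100, f² = 0.12, alpha = 0.05, four predictors, one record per participant. The test is not named. The overall F test of R² = 0 is assumed, being the natural reading of an f² quoted for a model with four predictors.

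**Formula.** With u model terms, v = n − u − 1 and λ = f² × n, power is the probability that a non-central F(u, v, λ) variable exceeds the central 95% point of F(u, v).

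**Step 1: the plan's own figure.** u = 4, v = 100 − 4 − 1 = 95, λ = 0.12 × 100 = 12.
- Power = 77.97%, against 80% stated.
- 80% needs n = 105, or f² = 0.1254 at n = 100.
- With f² = 0.125 (λ = 12.5), power is 79.8%. A value of 0.125 shortened to 0.12 would explain the gap.

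**Step 2: does another convention give 80%?** At n = 100 and f² = 0.12:

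| Variant | Power |
|---|---|
| λ = f² × v = 0.12 × 95 = 11.4 | 75.6% |
| Random rather than fixed regressors (simulated) | 76.9% |
| Overall test at alpha 0.10 | 86.5% |
| One coefficient carrying the whole f² | 92.9% |
| Two-degree-of-freedom posture test carrying the whole f² | 87.2% |
| One coefficient carrying the whole f², Bonferroni over four | 81.8% |

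None gives 80%. The nearest, the Bonferroni variant, does not match the stated p < 0.05.

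**Step 3: posture as two terms.** Three unordered categories need two indicators. Averaged to participant level, they become three shares of time that sum to one, so two are free. Then u = 3 + 2 = 5, v = 94, λ = 12.
- Power = 74.0%.
- 80% needs n = 113, or f² = 0.136 at n = 100.

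A single posture summary, such as the share of time lying down, keeps u = 4 and the 78.0% of step 1.

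**Step 4: complete-case analysis.** The article gives no loss rate, so the numbers analysable below are assumptions, with f² held at 0.12.

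| Analysable n (assumed) | Four terms | Five terms |
|---|---|---|
| 100 | 78.0% | 74.0% |
| 95 | 75.4% | 71.3% |
| 90 | 73% | 68% |
| 80 | 66.4% | 61.9% |

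**The case against.** The case against making much of this is fair in several respects.

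- On the article's own inputs the shortfall is about two percentage points, five participants, or 0.005 in f². The claim is worded as an expectation for effects of the stated size or larger. This stands: step 1 alone is close to rounding.
- Posture coding is a detail that an article may leave to a fuller document. One summary value per predictor is compatible with the text. This also stands: a reader might infer that the model certainly has five terms and that 74% is its power, but the article does not fix the coding. Its statement that no further predictors will be added does not settle how many terms posture uses.
- Losses may be modest. Values are averaged over the valid days available, so missed days alone need not remove a participant. Entry to the wearable sub-study requires having completed and adhered to the app phase. The requirement that the cohort exceed 100 suggests that 100 may mean the number needed in the analysis. These points weaken any forecast of large losses. However, the stated margin covers people who do not use the wearables; it does not mention wearers whose data are unusable.

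A reader might also infer that four coefficients will each be tested at 0.05, with low power for each and an inflated overall error rate. The article states no such rule: p < 0.05 appears only in the power sentence. That inference is not supported.

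None of these points restores 80% at f² = 0.12 with 100 participants.

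**Conclusion.** The stated power does not reproduce under either posture coding. It is 78.0% with four terms, a small shortfall, and 74.0% if posture takes two terms. At the stated effect, the chance of a missed finding is therefore 22% or 26% rather than 20%. Both figures assume the overall F test and 100 participants with complete data; any loss to unusable data lowers them.

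It would go too far to say that the design is seriously underpowered. The lower figures in step 4 rest on assumed losses, and the detectable effect at n = 100 moves only from 0.12 to 0.125 or 0.136. Severity is minor to moderate: a figure to correct and two definitions to state, with no threat to the validity of the primary analysis.

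**What to change.** Change the power statement in Primary endpoint analysis, and the Table 1 caption to match:

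1. State how posture enters the model and give the corresponding power at n = 100. With a single posture summary: 78% at f² = 0.12, or 80% at f² = 0.125. With posture as two terms: 74% at f² = 0.12, or 80% at f² = 0.136.
2. Say that the 100 counts Extreme Pain participants with complete data on all model variables, and that Healthy Controls who wear the sensors are not among them.
3. Say that the power refers to the overall F test of the model.

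The cost is wording and a slightly less favourable stated power. No extra patients and no change to the analysis are needed. The study status section reports that recruitment is ongoing and that no data have been analysed, so the change can be made before any result is known.
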